#### Primary Objectives

The primary objectives of this study are as follows:

To assess whether asthma control (assessed by exacerbation history, Asthma Control Questionnaire (ACQ), health care utilization, and short-acting beta-agonist (SABA) usage) is improved in MISSION SAAC patients compared with patients undergoing standard outpatient secondary asthma care at 6 months.To assess whether asthma control (assessed by exacerbation history, health care utilization, and SABA usage) is improved in MISSION RAAC patients compared with those who were eligible for MISSION but did not attend.To assess whether asthma control (assessed by exacerbation history, health care utilization, and SABA usage) is improved after attending the MISSION RAAC and SAAC.

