#### Description of Clinical Intervention and Treatment

Modern Innovative Solutions to Improve Outcomes in (MISSION) Severe Asthma is a novel service model pilot that took place in June and July 2014. MISSION was developed by asthma specialists from Portsmouth and Southampton asthma services.

The MISSION concept involved a “carousel clinic” which brings together all the assessments and investigations a patient requires into one clinic—the patient moved around each assessment or “investigation station” in a serial fashion. This allowed the research team to efficiently gather all the data required for both staff and the patient. This severe asthma patient journey was mapped and opportunities for improvement were identified such as earlier diagnosis by active case finding of at-risk patients, followed by a swift multidisciplinary assessment which meant patients could be seen sooner and assessed more effectively. Patients attending standard outpatient services undergo basic lung function, chest x-ray, and medical review. They are then referred for other tests or specialist opinions as required at different time-points

MISSION Severe Asthma identified patients with poorly controlled disease from general practice (GP) databases who had not been under secondary outpatient care in the last 12 months or who were not known to secondary care. The patients were then invited to Rapid Access Asthma Clinics (RAACs) for assessment at their GP surgery on a Saturday, at a time convenient for them. The clinics were held on Saturdays at a time better suited to the needs of asthma patients, many of whom are working or studying full-time.

The RAAC delivered a comprehensive asthma review including assessments of allergic status, airway inflammation, education, self-management planning, and smoking cessation leading to a written personalized 1-year asthma management plan for their GP providing clear treatment recommendations for those with uncontrolled but treatable asthma (see Figure 1). Treatment recommendations were in line with current asthma guidelines.

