#### Rationale for Study and Potential Impact

MISSION is a new and novel way of delivering highly specialized asthma care and has the potential to change the way asthma care is delivered across the United Kingdom as well as services for other long-term health conditions. The MISSION model is the first model of this type, and this study aimed to evaluate its success and compare the MISSION service with current care delivery. This will be done in several different ways. The study is a mixed methods evaluation of the new service comparing outcomes before and after the MISSION clinic using retrospective data analysis and prospective qualitative interviews. A control arm of patients not exposed to, but eligible for, the new MISSION clinic will also be included.

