### Sample Size

The study was powered to show a difference between the MISSION group and the primary care group for the primary outcome, exacerbation frequency. The sample size was based on an analysis of covariance (ANCOVA) approach, with the outcome being exacerbation frequency in the second 6-month period and with the exacerbation frequency in the first 6-month period being the covariate. Baseline data suggest a mean number of exacerbations for this group of 1.29, with an SD of 1.30. There is expected to be no change in exacerbation frequency between time periods for the primary care group, whereas it is anticipated that exacerbations in the MISSION group may reduce by 50% to 0.65 exacerbations. A correlation between the exacerbation rates in the 2 time periods of 0.5 is assumed. The primary care group will be larger, with an anticipated 3:1 ratio. To show a difference between groups with a 5% significance level and 90% power, it is calculated that 44 subjects in the MISSION group and 132 in the primary group are required.

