## Results

### Quantitative

The MISSION team screened GP records to identify uncontrolled asthmatics to invite to MISSION clinics. There were 369 patients identified who had one or more of the criteria that suggest uncontrolled or potentially severe asthma (high inhaled corticosteroid dose >500 mcg BDP (Beclomethasone Diproprionate) , 2 or more exacerbations in the last 12 months requiring steroids for more than 3 days, any hospital, ED or OOH contact in the last 12 months, and high SABA usage—>6 inhalers in the last 12 months or reduced lung function FEV1 ≤70%). All patients who were identified were approached for the MISSION project.

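### The third primary objective is a single-group before-after comparison in patients selected on recent high values of the same measures, so regression to the mean and season cannot be separated from a service effect; the no-change assumption for controls may also overstate power

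*Protocol article*

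**What the plan says.** - **Objective.** Primary Objectives lists three aims. The third is whether control, judged by exacerbation history, health care use and short-acting beta-agonist (SABA) use, "is improved after attending the MISSION RAAC and SAAC". The second is a controlled version for the Rapid Access Asthma Clinic (RAAC): whether control "is improved in MISSION RAAC patients compared with those who were eligible for MISSION but did not attend". Rationale for Study and Potential Impact also describes "comparing outcomes before and after the MISSION clinic using retrospective data analysis".
- **Selection.** Results, Quantitative, describes patients "who had one or more of the criteria that suggest uncontrolled or potentially severe asthma". The list includes "2 or more exacerbations in the last 12 months requiring steroids for more than 3 days", any hospital, emergency or out-of-hours contact in 12 months, and more than 6 SABA inhalers in 12 months. It also includes high inhaled steroid dose and reduced FEV1, which are not recent events.
- **Timing.** The service was "a novel service model pilot that took place in June and July 2014". The RAAC secondary outcomes use 6 months on each side of the clinic.
- **Sample size.** "There is expected to be no change in exacerbation frequency between time periods for the primary care group". The MISSION group is expected to fall by half, from 1.29 to 0.65.
- **Analysis.** Analysis of Endpoints gives a between-group ANCOVA on second-period exacerbations, adjusted for the first-period rate. It describes no single-group before-after test.

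**The concern.** When people are chosen because a fluctuating count was recently high, that count tends to be lower afterwards whatever is done. Here exacerbations, urgent contacts and SABA prescriptions serve both as entry criteria and as the outcomes of the third objective, and the 6-month window before the clinic lies roughly inside the 12-month look-back used for selection. Season adds a second difference: the window before runs from about December or January to June or July, and the window after covers the other half of the year. A single group cannot separate either influence from the service. The article mentions neither, and it ranks this objective as primary beside the two controlled ones.

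The same selection rule bears on the sample size. The invited non-attenders came from the same search, so an expectation that their rate stays at 1.29 is optimistic.

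**Working it through.** **1. The plan's own figure.** Inputs from Sample Size: mean 1.29, SD 1.30, MISSION mean 0.65, correlation 0.5, ratio 3:1, 5% significance (taken as two-sided), 90% power.

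- ANCOVA SD = 1.30 × √(1 − 0.5²) = 1.126; difference = 1.29 − 0.65 = 0.64.
- n = (1.960 + 1.282)² × 1.126² × (1 + 1/3) / 0.64² = 43.4, hence 44 and 132, as stated.
- SE = 1.126 × √(1/44 + 1/132) = 0.196; power = Φ(0.64/0.196 − 1.960) = 90.4%.

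The arithmetic is sound. What follows concerns the assumptions.

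**2. Single-group before-after test with no service effect.** The article gives no background fall, so 10, 20 and 30% are assumed. A two-sided paired test is also assumed, because none is specified. SD of change = 1.30 × √(2 × (1 − 0.5)) = 1.30. SE = 1.30/√44 = 0.196, or 1.30/√84 = 0.142 (84 is the number of RAAC attenders in Results). The chance of significance is Φ(fall/SE − 1.960) plus the negligible opposite tail.

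| Assumed fall | Exacerbations | n = 44 | n = 84 |
|---|---|---|---|
| 10% | 0.129 | 10% | 15% |
| 20% | 0.258 | 26% | 44% |
| 30% | 0.387 | 51% | 78% |

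The nominal rate is 5%.

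**3. Power of the planned ANCOVA if controls also fall.** Assume control means of 1.0 or 0.9 and a true 50% relative effect, so the differences are 0.50 and 0.45.

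- 44 and 132, SD kept at 1.30 (SE 0.196): Φ(0.50/0.196 − 1.960) = 72%; Φ(0.45/0.196 − 1.960) = 63%.
- 44 and 132, variance shrinking in proportion to the mean: SD = 1.30 × √(1.0/1.29) = 1.145, SE 0.173, power 83%; SD = 1.30 × √(0.9/1.29) = 1.086, SE 0.164, power 78%.
- 84 and 252 (all attenders consenting and 3:1 achieved, both assumed), SD 1.30: SE = 1.126 × √(1/84 + 1/252) = 0.142; power 94% and 89%.

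If the SD itself shrank in full proportion to the mean, the ratio of difference to SD would not change, and power would stay at about 90%. The loss therefore depends on how the SD behaves.

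**The case against.** The strongest reply is that the main inference is already protected. The study is powered on MISSION against primary care, those controls come from the same search, and the ANCOVA adjusts for the first-period rate. A fall common to both groups, from regression or season, cancels there. The article also says that the study is not a randomized trial and precedes a larger one. All of this stands for the second objective. It does not protect the third, which is listed as primary and has no comparator.

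Several stronger readings are tempting but unsupported:

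- *That the third objective is bound to show benefit from an inert service.* The chances in step 2 are inflated but well short of certainty, and no single-group test is specified.
- *That the untreated fall would match the anticipated 50%.* A gamma-Poisson model selecting only on two or more exacerbations can produce a fall of that order at a pre-period mean near 1.29. Those scenarios, however, have a pre-period SD of about 0.86 to 0.98 and a between-period correlation of about 0.06 to 0.13, against the plan's 1.30 and 0.5. Patients could also enter on steroid dose or lung function alone.
- *That a correlation of 0.5 means half of any selected excess disappears.* The plan's 0.5 is a planning value for the study groups. The halving rule needs the correlation in the unselected population and selection on that same 6-month count.
- *That the no-change assumption biases the comparison with controls.* It affects only the planned difference and the power. Differential regression would arise only if attenders and non-attenders differed in ways that first-period adjustment does not capture, which the article does not show.

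The power point is also softer than it looks, because 84 patients attended and all are to be approached.

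**Conclusion.** The concern holds in this form. As worded, the third primary objective cannot separate the service from regression to the mean or season. The direction of the regression effect is predictable, but its size is not derivable from the document. For assumed background falls of 10 to 30%, significant change with no service effect would appear in about 10 to 51% of paired tests with 44 patients and 15 to 78% with 84.

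The no-change assumption is a separate and lesser matter. It leaves the between-group ANCOVA unbiased but can overstate its power: about 72 to 83% at a control mean of 1.0 and 63 to 78% at 0.9, for a true halving at 44 and 132. In each range the lower figure keeps the SD at 1.30 and the higher lets the variance shrink with the mean. With 84 and 252 patients, power would be about 89 to 94% at SD 1.30. The control means, the SD behaviour and full consent are assumptions.

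**What to change.** 1. Report the single-group before-after results as descriptive only, and say that regression to the mean and season may contribute to them.
2. Answer the third objective from RAAC attenders against invited non-attenders over the same calendar windows, using the planned ANCOVA or a count model that adjusts for the first-period rate. An unadjusted difference in changes is not preferable: if the groups differ at baseline, it is itself open to differential regression to the mean.
3. In Sample Size, describe no change in controls as optimistic and add a power range over plausible control means, conditional on the relative effect, the SD and the numbers consenting.

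The cost is small. The pre- and post-period exacerbation, SABA and urgent-contact data for both groups are already among the secondary outcomes for RAAC and primary care patients, so this is mainly a change of wording. The stated power becomes less favourable, and since the clinics have already run, the restatement cannot enlarge the pool of attenders. The third objective loses its standing as an independent test, because its inferential content merges with the second.

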#### Secondary Objectives

To conduct a prospective qualitative study exploring patients’ experience, understanding and perceptions of their asthma as well as views on MISSION.To explore the acceptability of MISSION as a service model for patients, staff, and the NHS.To retrospectively compare a clinical case finding approach in primary care with a computer-assisted interrogation on primary care records.To assess the health economic impact of the MISSION service.To phenotype patients with uncontrolled or severe asthma in primary care and gain more information about the asthma population in Wessex.To assess whether asthma comorbidities are assessed in standard outpatient care.To assess waiting times and times to specialist referral in MISSION and standard outpatient care.

## Methods

### Study Design

A mixed methods observational study evaluating the new service, comparing outcomes before and after the intervention, and including a control arm of patients not exposed to, but eligible for, the new intervention is included. This will include analyses of the MISSION participants (attending both the RAAC and SAAC clinics), patients from the existing asthma service (from outpatient severe asthma clinics), and data from patients on GP records who were eligible to attend MISSION but did not (primary care patients). Finally, qualitative methods will be used to explore participant and health care professionals’ views on MISSION. Multimedia Appendix 1 summarizes the participants journey and the different populations under study.

The MISSION Severe Asthma project has not been designed as a randomized controlled trial (RCT) but designed to evaluate a novel service model (the intervention) in participants with uncontrolled and potentially severe asthma, to assess whether it is deliverable and acceptable by participants and health care professionals, and to explore the barriers that would need to be addressed before a larger RCT.

A patient advisor reviewed all patient-facing documentation for the study and will give advice and feedback on the structure of the qualitative interviews.

### Study Participants

Participants with uncontrolled or potentially severe asthma were identified from GP records by the MISSION team and new referrals to an asthma specialist clinic at Queen Alexandra Hospital between May and August 2014.

Study participants for qualitative interview will be recruited from patients who attended MISSION SAAC days and staff who attended MISSION RAAC or SAAC days. Qualitative one-to-one interviews will be held over the telephone.

Data for quantitative analysis will be collected from records made by the clinical team during the MISSION RAACs and SAACs and asthma outpatient clinics. GP records will be entered as usual by the GP. No extra data will be collected.

### Eligibility Criteria

The participant must meet all of the following criteria to be considered eligible for the study:

Male or female, aged 18 years or older.Is in one of the following population groups:Attended the MISSION RAAC orAttended the MISSION SAAC orIdentified as uncontrolled asthma by record searches and invited to the MISSION RAAC but did not attend “primary care patients” orHas been referred to the specialist asthma clinic at Queen Alexandra Hospital “outpatient severe asthma patients” orAttended the MISSION RAAC or SAAC as a health care professionalParticipant is willing and able to give informed consent for participation in the study.

### Primary and Secondary Endpoints and Outcome Measures for Quantitative Study

#### Primary Outcome Measure for All Patients

The primary endpoint is asthma control as measured by exacerbation frequency (defined as deterioration in symptoms requiring ≥30 mg prednisolone or equivalent for ≥3 days).

#### Secondary Outcome Measures for Modern Innovative Solutions to Improve Outcomes in Severe Asthma Assessment Clinic Patients and Outpatient Severe Asthma Clinic Patients

SABA use measured by the number of inhalers prescribed in 6 months pre- and post-MISSION or outpatient clinic.Exacerbation frequency (defined as deterioration in symptoms requiring ≥30 mg prednisolone or equivalent for ≥3 days) in 6 months pre- and post-MISSION or outpatient clinic.Health care usage costs for asthma and number of contacts (GP visits, emergency department [ED] or out-of-hour [OOH] attendances, hospital admissions, and emergency GP visits) over 6 months pre- and post-MISSION or outpatient clinic.Assessment of comorbidity (rhinosinusitis, anxiety and depression, dysfunctional breathing, gastro esophageal reflux, and obstructive sleep apnea) and method of assessment.Assessment of inhaler technique and recommendations for inhaler devices.Smoking cessation advice.Investigations performed during 6 months in secondary care, for example, full lung function, sputum induction, and performing a high-resolution CT scan of the chest.Time from GP referral to first clinic visit in secondary care.Time between first and second visit in secondary care.Time to appointment with other specialists for asthma-related comorbidity where indicated, for example, dietician, ENT, physiotherapist, psychologist, and CT imaging.Assessment of eosinophilic airways inflammation through measurement of fractional exhaled nitric oxide (FeNO).The frequency of nonattendance at clinic.

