### Recruitment

#### Modern Innovative Solutions to Improve Outcomes in Rapid Access Asthma Clinic and Severe Asthma Assessment Clinic Patients

All patients who attended the MISSION RAACs (quantitative) and SAACs (quantitative and qualitative) will be contacted by telephone to discuss the study and then, if they are interested, will be sent a patient information sheet (PIS) and consent form with a covering letter.

If the patient is unable to be contacted by telephone, they will be sent a covering letter from the MISSION team inviting them to take part in the study. They will be provided with a number to contact if they have any questions. They will be given the opportunity to read the PIS, and if they agree to take part in the study, they can return the consent form by post in a stamped addressed envelope.

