#### Outpatient Severe Asthma Patients

Patients who attended outpatient clinics as new referrals in June and July will be approached by telephone after being identified from the clinic attendance list. If the patient is willing, they will be sent a PIS and consent form to send back to the study team in a stamped addressed envelope.

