#### Analysis of Endpoints

The analyses will compare the study outcomes between the 4 study groups.

The primary outcome is exacerbation frequency. This outcome will be analyzed using ANCOVA, with the outcome variable being exacerbation frequency in the second 6-month period and the exacerbation rate in the first 6-month period treated as the covariate. Owing to the likely skewed distribution of the exacerbation frequency, it may be necessary to perform a log transformation of the outcome before analysis. Comparisons will be made overall between the 3 groups, and specifically between the MISSION group and each of the other 2 groups.

The analysis of secondary outcomes measured on a categorical scale during the second 6-month period will be compared between groups using Fisher exact test. Continuous variables will be compared between groups using analysis of variance, if found to be normally distributed, or the Kruskal-Wallis test, if not found to be normal.

Comparisons between groups will also be made accounting for the values during the first time period. ANCOVA will be used for continuous variables, whereas logistic regression will be used for binary outcomes.

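### Severe clinic versus outpatient comparison: first-visit nonattendance cannot be estimated from samples of attenders, the referral wait has no described start for MISSION patients, and later waits have no rule for visits not reached by 6 months

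*Protocol article*

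**What the plan says.** All references are to the protocol article.

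**Outcomes.** The secondary outcome list for SAAC and outpatient severe asthma patients includes "The frequency of nonattendance at clinic", "Time from GP referral to first clinic visit in secondary care", "Time between first and second visit in secondary care" and "Time to appointment with other specialists for asthma-related comorbidity where indicated". The Secondary Objectives include "To assess waiting times and times to specialist referral in MISSION and standard outpatient care".

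**Who is enrolled.** Eligibility Criteria define the SAAC group by attendance, and Recruitment agrees: "All patients who attended the MISSION RAACs (quantitative) and SAACs (quantitative and qualitative) will be contacted by telephone". Outpatients are described in two ways. Under Recruitment, new referrals who attended in June and July "will be approached by telephone after being identified from the clinic attendance list". Eligibility Criteria require only referral to the clinic, and the outpatient paragraph in Results takes all eligible new referrals until 20 are reached.

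**How MISSION patients arrived.** The description of the intervention says that they were found by searching general practice databases and invited to a Rapid Access Asthma Clinic (RAAC) at their GP surgery. Those with potentially severe, uncontrolled disease were invited to the SAAC at the hospital after a multidisciplinary meeting.

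**Data and analysis.** Notes are reviewed at 6 months, and information not found in them is marked as not assessed. The GP referral date is on the collection list for both groups. Under Analysis of Endpoints, "Continuous variables will be compared between groups using analysis of variance, if found to be normally distributed", with Kruskal-Wallis otherwise. The missing-data section says only that all data collected will be included.

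**The concern.** Nonattendance can be measured only among people who were due to attend. Once a group is formed from those who did attend, its first-visit nonattendance rate is fixed at zero and says nothing about the service. If only one of the two groups is formed in that way, the comparison is biased by design.

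A waiting time needs a start that exists in both groups and a rule for patients who are still waiting when observation ends. The referral wait lacks the first for SAAC patients. The second-visit and specialist waits lack the second.

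Waiting times are a stated secondary objective, and swifter assessment is part of the rationale for the service. A reader could therefore take an empty, one-sided or truncated comparison as evidence about access.

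**Working it through.** The plan gives no figure for nonattendance or waits, so there is none to reproduce. Its one sample size calculation, 44 and 132 for exacerbations in MISSION versus primary care, does reproduce (43.35 before rounding) but does not bear on this point.

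**1. First-visit nonattendance**

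| Outpatient frame | SAAC | Outpatients | Result |
|---|---|---|---|
| Attendance list (Recruitment) | 0% by definition | 0% by definition | Empty comparison |
| All referrals (Eligibility Criteria, Results) | 0% by definition | 0% or more | Can only favour MISSION |

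Neither frame gives an informative contrast. The one booking count in the article concerns the RAAC: 125 booked and 84 attended, so (125 - 84)/125 = 41/125 = 32.8% did not attend. Nonattendance is not a listed outcome for RAAC patients.

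**2. Start of the referral wait**

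- Outpatients: GP referral, then first hospital clinic.
- SAAC patients: record search, invitation, RAAC at the GP surgery, multidisciplinary meeting, invitation, SAAC at the hospital.

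No GP referral appears in the second sequence. It is also unclear whether the RAAC or the SAAC is the first visit in secondary care. Having the referral date on the data collection list does not create the event; where the notes hold none, the field is marked as not assessed.

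**3. Visits not reached by the 6-month review**

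A second visit or specialist appointment that has not happened has no duration, and neither ANOVA nor Kruskal-Wallis can use a patient without a value.

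Assume exponential waits with true mean m, a cut-off T = 6 months, and a proportion q unseen at T. Then m = T / ln(1/q), and the mean among those seen is m - T q/(1 - q).

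- q = 0.10: m = 6/ln 10 = 2.61; mean among seen = 2.61 - 6(0.10/0.90) = 1.94 months, 26% too low.
- q = 0.25: m = 6/ln 4 = 4.33; mean among seen = 4.33 - 6(0.25/0.75) = 2.33 months, 46% too low.

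Under the same model, for chosen true means:

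| True mean (months) | Seen by 6 months | Mean among seen (months) |
|---|---|---|
| 2 | 95% | 1.69 |
| 3 | 86% | 2.06 |
| 6 | 63% | 2.51 |
| 12 | 39% | 2.75 |

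True means of 3 and 6 months differ by 3 months; among those seen the difference is 2.51 - 2.06 = 0.45 months. If outpatient waits are longer, truncation shrinks the contrast. The article supplies neither the distribution nor the unseen proportion, so these figures are illustrations.

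**The case against.** The strongest reply is that these outcomes remain largely usable. The nonattendance outcome names no visit, and missed later appointments can be counted among people who attended first. That is correct, so a reader who infers that nonattendance as a whole is inestimable goes too far. It does not help for the first visit, and the outcome as worded leaves both visit and denominator open.

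Second, the outpatient sample is not consistently one of attenders. This also stands, but it replaces an empty comparison with a one-sided one.

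Third, the GP referral date is listed for both groups, so its absence for SAAC patients is an inference. It is, but from a pathway that the article describes in detail and that contains no referral.

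Fourth, nothing in the text says that unseen patients are excluded, and a condensed article may leave such handling to a fuller document. The article states no exclusion, but the tests it names cannot use a missing duration. The problem spares the time to first visit, since everyone enrolled as an attender has been seen. For the later waits it causes bias and does not prevent estimation. The likely direction is also conservative for MISSION, whose specialist assessments were largely held in the same clinic.

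Finally, patients with no second visit planned or no specialist indicated are not long waiters and must not be treated as censored. This is right and limits the remedy.

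**Conclusion.** The point holds within these limits:

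- First-visit nonattendance cannot be estimated from the enrolled samples. It is zero in both groups, or possible in outpatients only, depending on which outpatient frame applies. Eligibility Criteria, Recruitment and Results must be reconciled on that frame.
- The referral wait has no described origin for SAAC patients and is not comparable with the outpatient wait.
- Second-visit and specialist waits can be estimated, but probably with the longest waits missing. The 26-46% understatement rests wholly on assumed exponential waits and 10-25% unseen; the true size is unknown. If outpatient waits are longer, the bias shrinks the difference.

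Two further inferences are not supported. The article gives 22 patients identified for the SAAC and 20 who attended, from which a reader might infer 2/22 = 9.1% nonattendance; it does not say that all 22 were booked or why the numbers differ. A reader might also count attendance among the stated objectives, but the secondary objective covers waiting times and times to specialist referral only.

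The primary outcome is not affected. For secondary outcomes in groups of about 20, this should be corrected.

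**What to change.** 1. **Nonattendance.** Report first-visit nonattendance as aggregate counts over everyone booked: the RAAC (41/125), all SAAC invitees, and all new outpatient referrals booked in the same months. Report later missed visits separately, among attenders. Use one outpatient sampling frame throughout the article.
2. **Referral wait.** Start the MISSION clock at a defined date, such as the invitation, and say which clinic ends it. Report RAAC-to-SAAC time separately, and label neither interval as time from GP referral. A new start date does not make the groups comparable, so state that the origins differ from the outpatient origin and that the first-visit comparison is descriptive.
3. **Later waits.** Analyse second-visit and specialist waits as time-to-event (Kaplan-Meier, log-rank) from the decision or referral date, censored at the 6-month review, and only in patients with a second visit planned or a referral made. Specialist referral and appointment dates are already on the collection list.

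The cost is retrieving booking counts from the clinics, identifying from the notes who had a visit planned or a referral made, and slightly more analysis work. No extra patients are needed.
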